### Outcomes

All study patients will undergo review by two blinded observers (one orthopaedic registrar and one clinical research fellow) at 6 weeks, 6 months, 1 year, and 2 years following surgery. During these follow-up times, predefined clinical outcomes will be recorded by these observers using case report forms (CRFs). In addition, three independent observers (clinical research fellows) will collect radiological outcomes. It is not possible to blind observers recording radiological outcomes as different implant designs will be used within each treatment group. However, the three observers will independently calculate the accuracy of femoral and tibial implant positioning in each patient, and interobserver agreement for all radiological outcomes will be investigated using interclass correlation coefficients.

The following outcomes will be recorded in all study patients:
Accuracy of achieving the planned implant positioning as assessed using CT scans performed postoperatively at 6 weeks.Operating time (minutes)Time to hospital discharge (hours)Analgesia requirements during inpatient admission and postoperatively at 6 weeks, 6 months, 1 year, and 2 yearsPatient-reported outcome measures including Oxford knee score (OKS) and short form (SF-12), Western Ontario and McMaster Universities Arthritis Index (WOMAC), Knee injury and Osteoarthritis Outcome Score (KOOS), and University College Hospital (UCH) functional score during inpatient admission and postoperatively at 6 weeks, 6 months, 1 year, and 2 years.Health-related quality of life as measured using European Quality of Life questionnaire with 5 dimensions for adults (EQ-5D) preoperatively and postoperatively at 6 weeks, 6 months, 1 year, and 2 yearsMobilisation distance (metres) and use of mobility aids during inpatient admission and postoperatively at 6 weeks, 6 months, 1 year, and 2 yearsRange of movement (degrees) in the knee joint during inpatient admission and postoperatively at 6 weeks, 6 months, 1 year, and 2 yearsResource use and cost-effectiveness including comparisons between the two treatment groups relating to: Operating time, theatre efficiency, equipment and sterilisation costs, analgesia requirements, inpatient rehabilitation, time to discharge, outpatient follow-up, additional imaging costs, and need for further surgery.Complications

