All patients will undergo preoperative and postoperative CT scans of the knee joint using a standardised protocol within a dedicated research scanner in the study hospital. The CT scans will be uploaded in DICOM (Digital Imaging and Communication in Medicine) format and then loaded onto Mimics software (Materialise) to calculate the accuracy of implant positioning. Accuracy of implant positioning will be assessed by comparing differences in the target values in the preoperative plan to the achieved values in the postoperative scan. These outcomes will be used to calculate root mean square errors values for accuracy of femoral and tibial component positioning within the coronal, sagittal, and axial planes as described by Bell et al. [4]. The posterior condylar offset ratio (PCOR) and posterior tibial slope will be assessed using the methods described by Gaudiani et al. and Johal et al. respectively [13, 23].

The WOMAC, OKS, SF-12, EQ-5D, and KOOS are validated tools for the clinical assessment of patients after knee arthroplasty [11, 12, 17, 22, 39]. In addition, the observers will calculate the UCH knee score to assess overall, pain, function, and mobility [19]. This will help to overcome any potential ceiling effect with the OKS and WOMAC and facilitate further subgroup analysis in patients with high functional demands [19]. Each of these clinician- and patient-reported scores will be collected preoperatively at the time of consenting to the study and also postoperatively at 6 weeks, 6 months, 1 year, and 2 years after surgery.

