### Statistical analysis

The analysis of the per-protocol population will be considered the primary analysis. The differences between the CO UKA and RO UKA groups will be analysed by calculating the difference from baseline, per patient, and a two-sided confidence interval for the difference between the changes from baseline values will be calculated. This confidence interval will cover the true difference in the percentage change from baseline with a probability of 95%. The following statistical methods will be employed to analyse the data: descriptive statistics, independent *t* test, paired *t* test, analysis of variance, Fisher’s exact test, chi-square test, and graphical displays. Assumptions of normality will be tested with the D’Agostino test. Assumptions of homogeneity of variance will be tested with Levene’s test. If the distributional assumptions are (severely) violated, non-parametric techniques, such as Mann-Whitney’s test, will be employed. In the event that RO UKA is converted to CO UKA intraoperatively, analysis will be performed using the intention-to-treat population and the treatment actually received by the patients. Intraoperative conversion from RO UKA to CO UKA will be documented and presented and published as part of the study. The Bonferroni correction will be used to determine the level of significance due to multiple comparisons of secondary outcomes. Statistical significance is set at a *p* value < 0.05 for all analyses, and all statistical analysis will be performed using SPSS software version 26 (SPSS Inc., Chicago, IL, USA).

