### End of protocol treatment

Reasons for going off study protocol include:
Completion of last follow-up visit 2 years after surgeryPatient non-compliance or withdrawal (the reason for discontinuation will be recorded in the case report form)Intercurrent death

All patients included into this study are free to withdraw from the study at any time without compromise to their future treatment. On withdrawal, patients will revert to the standard follow-up regimen for routine (non-study) UKA at the study site. The end of study form will be completed and the reason for withdrawal documented. This form will also be completed if the patient is lost to follow-up or dies during the course of the study. Data to the point of discontinuation will be used for analysis.

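### Secondary scores measured at four visits are to be compared by change-from-baseline t tests and ANOVA, so the 1- and 2-year comparisons ignore the earlier scores of patients who have left

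*Protocol article*

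**What the plan says.** All references are to the protocol article.

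- **Statistical analysis** describes the between-arm comparison as "calculating the difference from baseline, per patient, and a two-sided confidence interval for the difference between the changes from baseline values will be calculated". It then fixes the tools: "The following statistical methods will be employed to analyse the data: descriptive statistics", followed by independent and paired t tests, analysis of variance, Fisher's exact test, chi-square test and graphs. Mann-Whitney is the fallback if distributional assumptions fail. No longitudinal model is named.
- **Statistical analysis** also sets the population: "The analysis of the per-protocol population will be considered the primary analysis".
- **Outcomes** schedules clinical review "at 6 weeks, 6 months, 1 year, and 2 years following surgery". For the scores it adds a baseline: "Each of these clinician- and patient-reported scores will be collected preoperatively at the time of consenting to the study". EQ-5D also has a preoperative value. Range of movement and mobilisation distance are listed for the inpatient stay and the later visits, with no preoperative value.
- **Outcomes** defines the primary outcome as a single assessment: "Accuracy of achieving the planned implant positioning as assessed using CT scans performed postoperatively at 6 weeks".
- **Sample size** allows for 10% attrition overall and says nothing about who leaves or from which arm.
- **End of protocol treatment** says of patients who leave: "Data to the point of discontinuation will be used for analysis". It does not say how.

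**The concern.** A change from baseline at 2 years exists only for a patient who has a 2-year value. A patient who attends at 6 weeks, 6 months and 1 year and then leaves contributes nothing to the 2-year t test, although three postoperative scores are on file and are correlated with the missing one. Adjusting the 2-year score for baseline does not help with this, because the relevant information lies in the intermediate visits.

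If leavers tend to be doing badly and leave more often from one arm, the patients remaining in that arm look better than the arm as randomised, and the later comparison is tilted in its favour. Function and quality of life are declared secondary objectives. The Background also criticises earlier studies for limited outcomes at short-term follow-up, so the later visits are where this trial means to add most.

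**Working it through.** **The plan's own figure.** With a difference of 2° and SD 4° (effect size 0.5), two-sided 5% and 80% power, the two-sample t test needs 63.77, so 64 per arm, or 128. The stated 128 is reproduced. It concerns femoral sagittal positioning on CT, so nothing below changes it.

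**Patients in a 2-year comparison.** At 10% attrition, 140 × 0.10 = 14 patients lack a 2-year value and 126 remain, about 63 per arm.

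**Approximate bias of the change-score t test, true difference zero.** Let *p* be the proportion lost in an arm, *m* the number of SDs by which leavers' scores at the visit driving their departure fall below the arm mean, *r₂* the correlation of that score with the 2-year score, and *r₀* its correlation with baseline. Those who remain then have a mean change shifted by

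m × p/(1 − p) × (r₂ − r₀)

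and the bias is the difference between arms in this quantity.

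The documents give none of *m*, *r₂*, *r₀* or the split of losses. Assume *m* = 1, *r₀* = 0.3 and *r₂* = 0.5 to 0.7, with loss driven by the observed 6-month score (missing at random). The last two columns come from simulations with 70 per arm under the same correlations.

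| Loss by arm | Difference in p/(1 − p) | Bias by formula (SD) | t test, simulated (SD) | Mixed model, simulated (SD) |
|---|---|---|---|---|
| 10% / 10% | 0.111 − 0.111 = 0 | 0 | within 0.01 of 0 | within 0.01 of 0 |
| 15% / 5% | 0.176 − 0.053 = 0.124 | 0.124 × 0.2 = 0.025 to 0.124 × 0.4 = 0.050 | 0.02 to 0.05 | 0.00 to 0.01 |
| 20% / 0% | 0.250 − 0 = 0.250 | 0.250 × 0.2 = 0.050 to 0.250 × 0.4 = 0.100 | 0.06 to 0.10 | 0.00 to 0.01 |

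A second simulation had loss driven by the 1-year score and 1- to 2-year correlations of 0.63 to 0.84. It gave 0.04 to 0.05 SD at 15%/5% and 0.08 to 0.12 SD at 20%/0% for the change score, and 0.005 SD or less for the likelihood model using all visits. Together these give the ranges of 0.02 to 0.05 and 0.06 to 0.12.

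**Two sensitivities.**
1. If the score driving loss is as strongly correlated with baseline as with the 2-year score (*r₂* = *r₀*), the formula gives zero. Simulations with all correlations equal at 0.4 or 0.6 gave at most 0.01 SD.
2. If loss is driven by the unobserved 2-year score itself (missing not at random) at 20%/0%, the t test is biased by 0.18 to 0.19 SD and the mixed model still by 0.12 to 0.18 SD. With all correlations equal at 0.4 or 0.6, the figures were 0.10 to 0.15 SD for the t test and 0.13 to 0.19 SD for the mixed model, so the model was then slightly worse.

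**Scale.** With a baseline-to-2-year correlation of 0.3, the change score has SD √(2 − 2 × 0.3) = 1.18. The standard error of the arm difference with 63 per arm is 1.18 × √(2/63) = 0.21 SD. A bias of 0.05 is 0.05/0.21 = 0.24 standard errors; 0.12 is 0.57.

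**Precision.** The mixed model reduced the standard error by about 1% to 5% in these simulations.

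**The case against.** Four points can fairly be made for the plan.

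1. **There is no contradiction with the End of protocol treatment section.** A reader might infer that the listed tests cannot honour the promise to use data up to discontinuation. The promise does not go that far. A patient who leaves after 1 year is still counted at 6 weeks, 6 months and 1 year, and nothing says that early values must inform later visits. Nor can case deletion by repeated-measures ANOVA be charged to the plan, since the article says only analysis of variance. This objection stands in full.
2. **Modelling and missing-data detail usually belong in an analysis plan, which is not shown.** This stands for the handling of missing data as such, and its absence is not the point here. But the article does not leave the method open: it specifies a change-from-baseline contrast and the tests that will be used. That choice can be assessed.
3. **Informative loss that differs by arm is an assumption.** Only 10% overall is given, and the planned blinding of patients makes loss driven by allocation less likely. This also stands, and it is why the bias is stated conditionally.
4. **A mixed model is no cure-all.** It relies on data being missing at random given observed scores, cannot restore patients excluded by a per-protocol population, and must sit alongside the non-parametric fallback for scores that may reach a ceiling. These points limit the remedy but do not remove the case for it.

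**Conclusion.** The point holds as a better choice of method for secondary outcomes. The tests fixed in the article make the 1- and 2-year comparisons rest on attenders alone, at a small cost in precision and with exposure to bias if informative loss differs between arms.

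The size is modest: about 0.02 to 0.05 SD at 15%/5%, 0.06 to 0.12 SD at the extreme 20%/0%, and about zero with equal loss. These figures rest on assumed correlations and loss driven by observed scores. They shrink to zero if that score is as closely related to baseline as to the 2-year value.

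Two stronger readings are not supported. The documents do not show that patients with poor scores will leave, or will leave more from one arm. And a mixed model does not by itself remove the problem, because under loss driven by unobserved scores most or all of the bias remains. The 6-week CT primary outcome and the sample size are unaffected.

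**What to change.** In Statistical analysis, state the following for each continuous outcome with several postoperative visits:

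- It is analysed with a linear mixed model for repeated measures in all randomised patients with available data, with terms for arm, visit and arm by visit and an unstructured covariance.
- Baseline by visit is added where a preoperative value is collected, that is, for the scores and EQ-5D. It is omitted for range of movement and mobilisation distance, for which the article lists none.
- The arm difference and its 95% confidence interval at each visit are read from the model. Per-visit t tests, or rank tests where the scale is badly skewed, are kept as descriptive.
- Because the model is valid only if data are missing at random given observed scores, a simple missing-not-at-random sensitivity analysis is added, for example shifting leavers' unobserved scores downwards by a range of amounts in one arm and then in both.
- The population for these outcomes is stated explicitly, since the article at present makes per-protocol the primary analysis.

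The cost is analysis wording plus one sensitivity analysis. No visit, measurement or patient is added, the named software fits the model, and the sample size does not change. The downside is reliance on the missing-at-random assumption, which the sensitivity analysis is there to probe.

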**Methods and analysis:**

This prospective randomised controlled trial will include 140 patients with symptomatic medial compartment knee arthritis undergoing primary UKA. Following informed consent, patients will be randomised to CO UKA (control group) or RO UKA (investigation group) at a ratio of 1:1 using an online random number generator. The primary objective of this study is to compare accuracy of implant positioning in CO UKA versus RO UKA. The secondary objectives are to compare the following outcomes between the two treatment groups: limb alignment, surgical efficiency, postoperative functional rehabilitation, functional outcomes, quality of life, range of motion, resource use, cost effectivness, and complications. Observers will review patients at regular intervals for 2 years after surgery to record predefined study outcomes pertaining to these objectives. Ethical approval was obtained from the London-Bloomsbury Research Ethics Committee, UK. The study is sponsored by University College London, UK.

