## Methods/design

### Objectives

The primary objective of this study is to compare accuracy of implant positioning in CO UKA versus RO UKA. Accuracy of implant positioning will be assessed by measuring differences in the planned implant position on preoperative CT scan versus the achieved implant position on postoperative CT scan. The null hypothesis is that there is no difference in accuracy of implant positioning between CO UKA versus RO UKA.

The secondary objectives are to compare the following outcomes between the two treatment groups:
Limb alignmentSurgical efficiencyPostoperative functional rehabilitationFunctional outcomesQuality of lifeRange of motionMobilisation distanceResource use and cost effectivenessComplications

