### Sample size

Using the study by Bell et al. assessing differences in accuracy of component positioning between conventional and robotic UKA, the mean difference in femoral sagittal component positioning was set at 2° and standard deviation assumed at 4° [4]. Using a two-tailed, two-sample *t* test with a power of 80% (1–β), significance level of 5%, and an effect size of 0.5, this study required 128 patients to detect this minimum difference between the two treatment groups. To account for 10% attrition in the sample size during follow-up, the sample size was set at 140 patients.

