## Discussion

Accuracy of component positioning and limb alignment are important prognostic variables that affect implant survival and time to revision surgery following UKA [5, 9, 38]. CO UKA is performed using manually positioned alignment guides, limited intraoperative data on knee kinematics, and handheld milling devices or sawblades for bone resection. However, these manual techniques are highly dependent on the skill and expertise of the operating surgeon. Surgeon-induced errors in implant positioning are the leading cause of premature implant failure and early revision surgery following UKA [29–32]. RO UKA uses a preoperative CT scan to create a virtual three-dimensional reconstruction of the patient’s osseous anatomy. The surgeon uses this virtual model to plan optimal bone coverage, implant positioning, and limb alignment. An intraoperative robotic arm then helps to execute this plan with a high-level of accuracy and reproducibility, and stereotactic boundaries limit bone resection to the predefined femoral and tibial haptic windows [4, 10, 26]. This prospective randomised controlled trial will include 140 patients with symptomatic medial compartment knee arthritis undergoing primary UKA. Following informed consent, patients will be randomised to CO UKA (control group) or RO UKA (investigation group) at a ratio of 1:1 using an online random number generator. Observers will review patients at regular intervals for 2 years after surgery to record predefined study outcomes pertaining to accuracy of implant positioning, limb alignment, postoperative rehabilitation, clinical progress, functional outcomes, cost-effectiveness, and complications. The following statistical methods will be employed to analyse the data: descriptive statistics, independent *t* test, paired *t* test, analysis of variance, Fisher’s exact test, chi-square test, and graphical displays. The findings of this study will provide an improved understanding of the differences in CO UKA versus RO UKA with respect to accuracy of implant positioning, limb alignment, patient satisfaction, functional outcomes, implant survivorship, cost-effectiveness, and complications.

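### The Bonferroni rule for secondary outcomes does not exempt complications, so it makes a real excess of harm harder to declare, and the next sentence leaves the threshold unclear

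*Protocol article*

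**What the plan says.** Under Objectives, the protocol article introduces its list with "The secondary objectives are to compare the following outcomes between the two treatment groups". Complications are the last of nine entries. The abstract's list of secondary objectives likewise ends with "range of motion, resource use, cost effectivness, and complications". The abstract's Discussion promises better understanding of differences in "functional outcomes, implant survivorship, cost-effectiveness, and complications", so a between-arm comparison of complications is intended for publication.

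The Statistical analysis section sets the multiplicity rule: "The Bonferroni correction will be used to determine the level of significance due to multiple comparisons of secondary outcomes". It names no family, gives no divisor and makes no exception for complications. The next sentence begins "Statistical significance is set at a *p* value < 0.05 for all analyses". For categorical outcomes the listed methods include "Fisher’s exact test, chi-square test, and graphical displays". The only confidence interval described in that section is for change from baseline, a quantity that complications do not have.

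The Adverse events section separately has the sponsor and the DSMB monitor safety on unblinded data. It states no significance threshold and does not refer to the Bonferroni rule.

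**The concern.** Bonferroni protects against false positives. That is reasonable for a long list of efficacy and cost outcomes, where the worry is claiming a benefit that is not there. For harm the more serious error usually runs the other way: failing to notice a real excess. When complications share a Bonferroni family with function, quality of life and cost, every further outcome in the family makes an excess of complications harder to declare, although those outcomes have nothing to do with safety.

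At stake is the published comparison. An excess whose ordinary 95% confidence interval excludes zero could be reported as not significant. The adjacent p < 0.05 sentence adds a second problem: two analysts following the same paragraph could reach opposite statements about the same complication table.

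**Working it through.** **Reproducing the plan's own figure.** The Sample size section uses a "two-tailed, two-sample *t* test with a power of 80% (1–β), significance level of 5%, and an effect size of 0.5", and states that "the mean difference in femoral sagittal component positioning was set at 2° and standard deviation assumed at 4" degrees. The effect size is 2/4 = 0.5. The normal approximation gives n per arm = 2 × (1.960 + 0.842)² × (4/2)² = 62.8, so 63. The noncentral t calculation gives 63.77, so 64 per arm and 128 in total, as stated. For attrition, 128 × 1.1 = 140.8 and 128/0.9 = 142.2; the stated 140 is close to both. The sample size therefore rests on implant position alone. With 1:1 allocation it gives 70 per arm, or 63 per arm after 10% loss.

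**Inputs that must be assumed.**
- *Divisor:* not stated. Counting the nine listed objectives gives 0.05/9 = 0.0056. Counting each score and visit would give a larger divisor. For illustration, 40 tests would give 0.05/40 = 0.00125.
- *Complication rates:* not stated. The nearest figures, in the Background, are 2-year failure rates of 1.2% and 3.1% and revision rates of 5% and 9%. These are different events and serve only as a rough guide to the range.

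**Method.** Exact power is the sum, over all pairs (a, b) with b/n above a/n and two-sided Fisher p below alpha, of Bin(a; n, p₁) × Bin(b; n, p₂).

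| Assumed rates | 70/arm, 0.05 | 70/arm, 0.0056 | 63/arm, 0.05 | 63/arm, 0.0056 |
|---|---|---|---|---|
| 3% v 9% | 18% | 4% | 15% | 2% |
| 5% v 15% | 41% | 14% | 35% | 11% |
| 9% v 27% | 75% | 44% | 69% | 37% |
| 10% v 20% | 30% | 9% | 26% | 7% |
| 10% v 30% | 81% | 52% | 76% | 44% |
| 15% v 45% | 97% | 85% | 95% | 79% |

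With the illustrative divisor of 40, power for 5% v 15% at 70 per arm is 6%.

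**Where a tripling is missed more often than not (70 per arm).** At 0.0056 this holds while the control rate is below about 9.7% (Fisher) or 8.8% (uncorrected chi-square). At 0.05 it holds only below about 5.9% or 4.8%. At 63 per arm and 0.0056 the limits are 10.8% and 9.7%.

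**One table, two readings.** For 4/70 v 15/70, Fisher p = 0.012. The risk difference is 11/70 = 15.7 percentage points, with a Newcombe 95% interval of 4.4 to 27.2. The result is significant at 0.05 and not significant at 0.0056. Against 4 events in one arm, the other arm needs 13 events at 0.05 and 17 at 0.0056.

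**Splitting the cause for 5% v 15%.** The miss rate is 100 − 41 = 59% at 0.05 and 100 − 14 = 86% at 0.0056. Sample size alone accounts for 59 points, and the correction adds 27.

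**The case against.** The strongest reply has four parts.

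1. *The tightened level may not apply.* The p < 0.05 sentence can be read as a plain threshold, in which case the example table above is significant. It can equally mean Bonferroni-adjusted p values compared with 0.05. The text does not settle this, so a reduced level cannot be called the only stated rule. This stands, and is why the two sentences need reconciling.

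2. *The divisor and rates are not in the document.* Bonferroni might be meant within sets of related scores and visits, which would leave a single complications test little affected. Defining the family, and the effect measure for adverse events, is commonly left to an analysis plan that is not shown. This stands as a limit on the numbers, and no finding is made of the missing definition or of a missing safety margin. It does not remove the point that the stated rule covers secondary outcomes without an exception for safety.

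3. *The small sample does most of the damage at low rates.* This is correct: 3% v 9% has only 18% power at 0.05. Removing Bonferroni will not make such differences significant, which is a reason to report an interval and not rely on a threshold.

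4. *Safety is monitored elsewhere, and descriptive statistics are listed.* DSMB review is not tied to this rule, so patient protection during the trial is not in question. The point concerns the final reported comparison only.

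A reader might infer that even a tripled complication rate would usually go undeclared, or that the comparison could not reveal harm at all. Neither follows. At 10% v 30% power is 52% under the divisor of nine, and at 15% v 45% it is 85%. Nor does the protocol say that non-significance will be called safe.

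**Conclusion.** The point holds in a limited form. As written, the multiplicity rule covers complications and makes a real excess harder to declare, while the adjacent sentence leaves the operative threshold unclear. If the divisor is nine and the rates are 5% v 15%, Fisher power at 70 per arm falls from 41% to 14%. A tripling is missed more often than not only if the control rate is below about 10%. If plain 0.05 applies, that limit drops to about 5% to 6% and the loss from Bonferroni disappears. Divisor and rates are assumptions, and low power at low rates is largely a matter of sample size. This is a cheap improvement to the analysis wording and not a flaw that threatens the trial's primary conclusion.

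**What to change.** Amend the Statistical analysis section as follows.

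- Limit the Bonferroni correction to the secondary efficacy and cost outcomes.
- Report complications, including further surgery when it is counted as a complication, as counts per arm and a risk difference between arms with an unadjusted 95% confidence interval.
- State that a non-significant test is not evidence of equal safety.
- Reconcile the two threshold sentences, for example by saying that 0.05 applies to the primary outcome and to Bonferroni-adjusted p values for the secondary outcomes that remain in the family.

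This takes a few sentences and needs no extra patients or data. The cost is a higher chance of a false-positive harm signal. The unadjusted interval may also show openly that a trial of 140 patients cannot exclude a sizeable excess.

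### Plain Bonferroni is fixed for secondary outcomes measured at up to five visits with no deciding visit named; Holm's step-down over one named contrast per outcome controls the same error and loses less power.

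*Protocol article*

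**What the plan says.** The multiplicity rule is one sentence in the Statistical analysis section: "The Bonferroni correction will be used to determine the level of significance due to multiple comparisons of secondary outcomes". It gives no divisor and does not say which comparisons form the family. The same section also says "Statistical significance is set at a *p* value < 0.05 for all analyses".

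The Objectives section opens its list with "The secondary objectives are to compare the following outcomes between the two treatment groups" and names nine headings. The Outcomes section turns these into measurements. The patient-reported scores (OKS, SF-12, WOMAC, KOOS and the UCH score) are listed as "functional score during inpatient admission and postoperatively at 6 weeks, 6 months, 1 year, and 2 years", which is five times after surgery. Analgesia, mobilisation distance, use of mobility aids and range of movement follow the same five times. EQ-5D has four times after surgery. A later paragraph of the same section gives the five scores a preoperative and four postoperative collections, with no inpatient one, so their number of postoperative comparisons is four or five. No visit is singled out for any repeated outcome.

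The only power statement is for the primary outcome: "two-tailed, two-sample *t* test with a power of 80% (1–β), significance level of 5%, and an effect size of 0.5".

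**The concern.** Bonferroni divides the 5% level by a number of tests, so its effect depends on that number. Here the measurements are mostly repeats of one instrument on the same patients, and such repeats are correlated. Dividing by every visit spends most of the significance level on near-duplicates. Dividing by outcomes while testing every visit leaves the repeats uncorrected. The two counts give thresholds of about 0.001 and 0.004, so a secondary result with p = 0.002 would be significant under one and not under the other.

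The trial's statements on function, quality of life and rehabilitation all rest on secondary outcomes. Plain Bonferroni also gives away power that Holm's step-down keeps at no cost in error control.

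**Working it through.** **Inputs from the protocol.** Two-sided 5%, 80% power, effect size 0.5 and 128 evaluable patients, so 64 per arm (Sample size); the outcomes and visits (Outcomes).

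**Inputs assumed.** The effect size for secondary outcomes and the correlation between tests. The protocol gives neither, so ranges are shown.

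**1. The protocol's own figure.** "the mean difference in femoral sagittal component positioning was set at 2° and standard deviation assumed at 4" degrees, so d = 2/4 = 0.5. For a two-sample t test with n per arm, the noncentrality is d√(n/2) on 2n − 2 degrees of freedom. With n = 64 it is 0.5 × √32 = 2.83 on 126 degrees of freedom, and power at 0.05 is 80.1%. The stated 128 is reproduced.

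**2. Counting the tests.**

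| Outcome | Comparisons |
|---|---|
| Operating time | 1 |
| Time to discharge | 1 |
| Analgesia | 5 |
| Five patient-reported scores, 4 (or 5) visits each | 20 (25) |
| EQ-5D | 4 |
| Mobilisation distance | 5 |
| Mobility aids | 5 |
| Range of movement | 5 |
| Complications | 1 |
| **Total** | **47 (52)** |

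Distinct outcomes in this list: 1 + 1 + 1 + 5 + 1 + 1 + 1 + 1 + 1 = 13. Limb alignment, resource use and subscales are left out of both counts.

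**3. If every comparison is counted.** The thresholds are 0.05/47 = 0.00106 and 0.05/52 = 0.00096. Power comes from the formula in step 1 with 64 per arm:

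| Assumed difference (SD) | Divisor 13 | Divisor 47 | Divisor 52 |
|---|---|---|---|
| 0.3 | 11% | 5% | 5% |
| 0.5 | 46% | 31% | 30% |
| 0.6 | 67% | 52% | 51% |
| 0.8 | 94% | 88% | 87% |

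**4. If only outcomes are counted but every visit is tested.** The threshold is 0.05/13 = 0.00385. For independent tests, family-wise error is 1 − (1 − 0.05/13)^m:
- m = 47: 16.6%
- m = 52: 18.2%

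For correlated tests, each statistic was simulated as √ρ·U + √(1−ρ)·E, with a shared normal U and a separate normal E. A rejection is any absolute value above 2.89, the two-sided critical value for 0.05/13. In 200,000 draws:
- ρ = 0.5: 9.4% (m = 47) and 10.0% (m = 52)
- ρ = 0.8: 3.9% and 4.2%

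The ρ = 0.8 case requires every outcome to correlate at 0.8 with every other, not only visits of the same score.

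**5. Holm against Bonferroni.** Holm orders the p-values, tests the smallest at 0.05/m, the next at 0.05/(m − 1), and so on, stopping at the first failure. Its first step is Bonferroni's threshold and later steps are looser, so it rejects everything Bonferroni rejects. It controls family-wise error under any dependence, as Bonferroni does. Simulated average power per truly different outcome, with nine outcomes, d = 0.5, 64 per arm, correlation 0.5 and normal statistics:
- five of nine differ: 52% (Bonferroni) against 56% (Holm)
- all nine differ: 52% against 63%

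The 52% is the normal-approximation counterpart of 50.5% from the noncentral t at 0.05/9.

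**The case against.** The strongest reply is that the missing divisor and deciding visit are details an analysis plan usually fixes, and that plan is not shown. This stands: their absence from a condensed article is not in itself a fault. Bonferroni is also a valid procedure. The rule speaks of multiple comparisons, so the plain reading is that the divisor is the number of comparisons made, and then the family is controlled at 5%.

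Two stronger readings are tempting, and the document supports neither.

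- **A reader might infer that each secondary test has about 30% power.** That figure borrows 0.5 SD from femoral component position and needs a divisor near 50. Other effect sizes give 5% to about 88%. The protocol promises power only for the primary outcome, so low power elsewhere breaks no commitment.
- **A reader might infer that the secondary family is not controlled at 5%.** That requires dividing by outcomes while testing every visit, which no section says will be done. Dividing by nine would make the inflation look larger, but nine counts objective headings. The outcomes behind the test count number 13, and at a correlation of 0.8 throughout the error is about 4%.

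It can also be said that Holm's gain is modest and a matter of preference. The gain is modest when about half the outcomes differ (four percentage points). It is still free, because the error control is the same.

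**Conclusion.** The point holds as an improvement to a method the protocol has chosen; the rule itself is valid. Plain Bonferroni is a poor fit to correlated repeat visits. Counted over all 47 to 52 comparisons, it sets a threshold near 0.001 and leaves about 30% power at 0.5 SD. Counted over about 13 outcomes with all visits tested, family-wise error ranges from about 4% to 18% with the assumed correlation. Both sets of figures rest on assumed effects or correlations and show what is at stake; they do not establish an error rate for this trial.

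The firm part needs no such assumption: Holm never rejects less than Bonferroni and has the same error guarantee. One contrast per outcome also removes the dispute over counting visits. Its first threshold would be 0.05/13 = 0.0038, where power at 0.5 SD is 46% even before Holm's later steps, against 30–31% when every visit is counted.

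**What to change.** Reword the multiplicity sentence in the Statistical analysis section to do four things:

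- Name one deciding contrast per secondary outcome before any results by arm are seen: either one stated visit or one average over visits from a repeated-measures model.
- State that the correction runs over those contrasts only, and give their number.
- Use Holm's step-down in place of plain Bonferroni.
- Report all other visits as estimates with 95% confidence intervals and no significance claim.

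In the same edit, say that the general 0.05 level is the family level for secondary outcomes, so that it cannot be taken as an uncorrected per-test threshold.

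The cost is wording only, with no new data, visits or patients. The downside is that visits not chosen as the contrast carry no significance claim, so the investigators must decide in advance which time matters most for each outcome.
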